
#### ii) Cost-effectiveness outcomes

An economic evaluation will be conducted from the perspective of the society and the Health Service comparing the EIRA intervention vs. the usual care group at 12-months post-intervention.
*Outcome measure*
Incremental cost per quality-adjusted life years (QALYs) gained will be calculated. QALYs will be measured using the Spanish tariffs of the EuroQol-5D questionnaire [53]. The following costs will be taken into account: hospital care (emergency visits and stays), secondary care (visits to specialists), primary care (visits to physician and nurse), social care services (visits to social worker), outpatient diagnostic tests, medication use, group sessions attended, community resources used and loss of productivity (days off work). This information will refer to the last 12 months prior to study entry and to the subsequent 12 months. Use of healthcare resources and lost productivity will be assessed through the patients’ clinical history and also the Client Service Receipt Inventory [65]. Information on the use of medicines (active substance, dose, and units supplied) will also be collected. The unit costs of public healthcare services will be obtained from the Official Bulletin of the Government. Costs of privately funded services will be obtained from published tariffs. The mean price per milligram of active substance will be calculated using the prices of the generic versions of all the presentations as reported in the Spanish Vademecum. Productivity losses will be calculated based using information on the minimum and average daily wage in Spain [66].

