#### Cost-effectiveness of intervention

The incremental cost-utility ratio will be estimated. It will be obtained by calculating the relationship between the cost of the intervention and the usual care, and its consequences expressed in QALYs.

The cost-utility analysis will refer to the incremental analysis as a result of the quotient between the cost difference of the intervention with respect to usual care, and the change in the results of the difference of cost of the intervention over the difference of cost of the usual care (differences in QALYs). Generalised linear models will be used to model costs and QALYs. Due to the biased distribution of costs, the gamma distribution is usually the most suitable to analyse cost data [73]. The models to estimate differences in costs and QALY will be adjusted for the differences between the two groups in terms of the study covariates. Confidence intervals will be estimated using bootstrap techniques [74] which have the advantage of not having to accept parametric assumptions and whose estimations of standard errors are currently considered very useful and robust in the context of clinical trials [75].

Cost-effectiveness acceptability curves will be obtained based on the theory of net incremental benefit and different hypothetical values of the maximum availability to pay for health gains. These curves represent the probability that an intervention will be more cost-effective than other alternatives and summarise the uncertainty in cost-effectiveness analysis.

Simple sensitivity analyses will be performed. One or more parameters of the evaluation that generate uncertainty will vary in order to see how they affect the robustness of the results. We will conduct a complete case analysis, analysis changing the unit cost of services, andan analysis using the average wage instead of the minimum wage. If the results are sensitive to their variations, simultaneous sensitivity analyses will be performed adjusting for all the sensitive parameters by multiple regression methods.

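### The simultaneous sensitivity analysis of the cost-utility result is to adjust by regression for unit costs and wage, which are inputs to the cost and not covariates; read as written, it says nothing about joint robustness

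*Protocol article*

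**What the plan says.** The relevant text is in the protocol article, Analysis, Cost-effectiveness of intervention. Simple sensitivity analyses come first: "One or more parameters of the evaluation that generate uncertainty will vary in order to see how they affect the robustness of the results". Three are named. Two stand together, "We will conduct a complete case analysis, analysis changing the unit cost of services", and the third is an "analysis using the average wage instead of the minimum wage". If the results respond to these changes, a further step follows: "simultaneous sensitivity analyses will be performed adjusting for all the sensitive parameters by multiple regression methods".

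The section on cost-effectiveness outcomes says where the inputs come from. For public services, "The unit costs of public healthcare services will be obtained from the Official Bulletin of the Government"; productivity losses use "information on the minimum and average daily wage in Spain".

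The base case is already a regression analysis. "Generalised linear models will be used to model costs and QALYs", with a gamma distribution in view for costs, and the models "will be adjusted for the differences between the two groups in terms of the study covariates". Confidence intervals come from the bootstrap, and acceptability curves are planned.

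**The concern.** A multi-way sensitivity analysis asks how the result moves when several uncertain inputs change together. To answer that, the inputs have to be changed and the costs recomputed. Adjustment in a regression does something else: it holds constant a characteristic that differs between participants. A tariff or a national wage is not such a characteristic. It is a multiplier applied to everyone's visits or days off before the cost outcome exists.

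Cost-effectiveness is part of the first primary objective. The simultaneous step is triggered only when the one-way analyses have shown the result to be fragile, which is when a sound joint analysis is most useful. If the step is carried out as worded, it adds a line to the report and no information.

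**Working it through.** The plan gives no figure to reproduce here, so the check is algebraic, followed by an illustration on assumed data.

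**Algebra.** Take a simplified cost for participant *i*: C_i = u x visits_i + w x days off_i, with *u* the unit cost and *w* the daily wage. Put *u* and *w* into the linear predictor next to the arm:

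b0 + b1 x arm_i + b2 x u + b3 x w = (b0 + b2 x u + b3 x w) + b1 x arm_i.

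Only the sum in brackets can be identified. The coefficients b2 and b3 are not estimable, and b1 is unchanged. The same holds for a gamma model with a log link, because the argument concerns the linear predictor.

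**Inputs of the illustration.** From the document: 3640 participants and 30% loss, so 3640 x 0.7 = 2548. Everything else is assumed:
- mean visits 6 (control) and 5.7 (intervention);
- 20% of participants with days off, mean 20 and 18 days;
- QALY difference 0.01;
- a random 80% of participants complete;
- unit cost 40 in the base case, 32 and 48 as alternatives;
- minimum wage 25, average wage 60.

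Differences are plain differences in arm means; clustering is ignored because it does not bear on the point.

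**Adjusting as worded (u = 40, w = 25).** Intercept and arm alone: rank 2 of 2 columns, cost difference -36.76. With unit cost and wage added: rank 2 of 4 columns, cost difference -36.76.

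**Recomputing jointly (3 unit costs x 2 wages x 2 analysis sets = 12 combinations).**

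| Unit cost | Wage | Cost difference, all | Cost difference, complete cases |
|---|---|---|---|
| 32 | 25 | -33.04 | -31.53 |
| 32 | 60 | -58.48 | -55.53 |
| 40 | 25 | -36.76 | -35.13 |
| 40 | 60 | -62.20 | -59.13 |
| 48 | 25 | -40.48 | -38.73 |
| 48 | 60 | -65.92 | -62.72 |

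The QALY difference is 0.0110 for all participants and 0.0119 for complete cases. The cost difference runs from -31.5 to -65.9, and covariate adjustment shows none of this.

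**Other ways to bring regression in.**
- *Analysis set.* This is not a constant of the calculation. A completeness indicator varies between participants and can be fitted (rank 3 of 3). Adjusting for it keeps the incomplete cases in the model, so it is not a complete-case analysis.
- *Stacking the data under both wages, with wage as a covariate.* Each participant then appears once under each wage, so wage is orthogonal to arm. In a linear model the arm coefficient is the average, (-36.76 - 62.20)/2 = -49.48, which conceals the spread between the two.
- *Regression across recomputed scenarios.* With 500 scenarios, net benefit regressed on unit cost and wage has full rank (3 of 3) and can be fitted. It needs the joint recalculation first, and the inputs are then explanatory variables, not adjusters.
- *Regional tariffs.* If the bulletin's tariffs differ between the seven Autonomous Communities (an assumption), unit cost varies between participants, but only with region. Adjusting for it would be regional adjustment, not a sensitivity analysis.

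**The case against.** The best defence is that the clause is loose wording for a sound procedure. The text does not state the outcome, regressors or unit of observation of the regression. The preceding sentences already allow more than one parameter to vary, and the base-case models are themselves regressions. Changing the sensitive inputs together and rerunning those models would be a valid simultaneous analysis. So would a regression across recomputed scenarios. The article is also a condensed account, and scenario ranges and model form may properly sit in a fuller plan.

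Much of this stands. It would be wrong to say that regression can have no place in the step, and the missing ranges are no fault. But the article does not leave the method open: it names adjustment for the sensitive parameters, and neither workable procedure is described. Because the main models already adjust for covariates, the natural reading is that the parameters join that list.

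A reader might also infer that the step would pull the incremental cost toward zero, through adjustment for visits or days off, which are components of the cost arising after randomisation. The document does not support this. It lists complete cases, unit costs and wage as the things to vary, and nowhere proposes adjusting for resource quantities. With constant covariates the arm difference does not move at all.

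**Conclusion.** The article names an unsuitable method for a conditional step of the economic analysis. For unit costs and wage, adjustment as worded is empty: not estimable, or without effect on the arm difference. For the analysis set, it answers a different question from the complete-case analysis.

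The consequence is a step that does not inform, not a distorted estimate. The base-case ratio, bootstrap intervals, acceptability curves, one-way analyses and the effectiveness result are untouched, so this is a minor improvement.

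The conclusion rests on the literal reading of the clause and on unit costs and wage being common to all participants, or at most differing by region. The sizes in the table depend on assumed resource use and prices; neither their sign nor their magnitude is a forecast for this trial.

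**What to change.** Replace the clause. The trigger can stay as it is. The new text could run along these lines:

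> When one-way results are sensitive, each participant's costs and QALYs are recomputed with the sensitive inputs changed jointly (sets of unit costs x minimum or average wage x imputed or complete-case data). The same adjusted cost and QALY models and the same bootstrap are rerun for each combination. The range of the incremental cost-utility ratio and of the probability of being cost-effective is reported.

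If the authors intended a regression across recomputed scenarios, they should say so and state its outcome, regressors and unit of observation.

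The cost is some extra computing, for example 12 runs with bootstrap for a 3 x 2 x 2 grid. No new data are needed.

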#### Effectivenessof implementation strategy

The assessment of the implementation strategy will be carried out through qualitative and quantitative methodologies. We will evaluate it in terms of:Implementation outcomes (stated earlier).Determinants.Characteristics of PHC centres and professionals will be analysed as determinants of implementation. Furthermore, three focus groups (one of the health professionals and two of participants) will be conducted in each PHC centre in the post-implementation stage. Sampling will be theoretical (discursive plurality). Sessions will be transcribed in an anonymous way. A thematic content analysis will be done and data will be coded in accordance with CFIR constructs [76]. Moreover, these results will be analysed quantitatively. CFIR constructs will be scored following standard criteria that will reflect the influence of the construct on the implementation (positive or negative) and its magnitude (between 1 and 2) [77].*Level of development*. The level of development of each of the implementation strategies will be determined from an online database. Updating of this database will be carried out by the implementation facilitator. Likewise, we will develop logistic regression models in which the dependent variable will be the effectiveness of the intervention, considered as a positive change in any of the three behaviours studied. The independent variables will be the quantitative measures of the results of the implementation and the degree of implementation of the different strategies. The purpose of these analyses is to model the relationship between the implementation variables and those of effectiveness. On the other hand, the influence and the magnitude of the determinants of the implementation and the results will be established through multivariate models.

## Discussion

Implementation research experts point out that the future studies should be addressed to the sustainable integration of interventions into health care delivery systems [78]. EIRA study is in line with these recommendations as it seeks to achieve changes to promote health through PHC professionals (individual and organisational changes). These changes will reduce the research-practise gap and provide populations health benefits.

To achieve a behaviour change is more feasible when combining individual, group and community interventions [79]. That is why the EIRA study has considered health promotion interventions at these three levels. The study has a person-centred approach that seeks to improve his/her self-efficacy to adopt and sustain healthy behaviours. Because of that, motivational interviewing and information technologies will be used. In addition to focusing on the person, the study has a community-centred focus which aims to increase intersectoral linkages and participatory forums at the local level [30].

However, EIRA study will carry out in real-world PHC setting with a broad range of significant implementation challenges. Implementation of health promotion interventions in PHC is not an easy task, especially after the overall economic crisis, the increasing workload of health professionals and the multiple existing barriers. The previous phases of study enabled to identify some of these barriers and introduced changes in the design of the intervention to improve its feasibility such as reduction of the screening for entrance into the study, incorporation of training on motivational interview and increase in the practical training, extension of the period of follow up, etc. Therefore, the use of the methodology proposed by Medical Research Council has facilitated the design of this study, though some added difficulties have featured. This new approach in research entails an active role of the different stakeholders to create a feasible intervention. This is a big change in the research culture in the present situation of Spanish PHC. Managers, professionals, and researchers are more familiar with the classical methods (clinical trials, for instance) where different factors have to be under control, but not with the uncertainties and variability that implies the adaptation of complex interventions to different PHC centres, and the crucial participation of different stakeholders.

EIRA study will determine the effectiveness and cost-effectiveness of a complex multiple risk intervention and will provide a better understanding of implementation processes of health promotion interventions in this PHC setting. It may contribute to increase knowledge about the individual and structural barriers that affect implementation of these interventions and to quantify the contextual factors that moderate the effectiveness of implementation. This study, therefore, not only entails the evaluation of a complex intervention in PHC but also a change in the evaluation culture of the Spanish research in PHC. The redIAPP, the research network in charge of this study, is introducing this important research perspective in its present scenario.

## Abbreviations

CFIR: Consolidated Framework for Implementation Research
CRF: Case Report Form
PHC: Primary Health Care
QALY: Quality-adjusted life year
SMS: Short Message Service
TTM: Transtheoretical Model
